## 2. Method and Materials

### 2.1. Study Design

The design of this study is a cross-sectional examination or a clinical and observational study of children in the first, fifth, and ninth grades in Danish primary schools. The schools will be selected randomly by their socioeconomic profiles. Our focus will be on analyzing their clinical status, pain levels, foot dimensions and pressure, and footwear. Specifically, we plan to evaluate misalignments, malpositions, deformities, skin and foot hygiene, and the rotational status of the lower leg, as well as the range of motion in the lower extremities of the children. These data will serve as a reference for the foot demographics and provide insights into the health of children’s feet. We will enquire about foot health and quality of life using PROMs, and we will measure foot dimensions using 3D scanning techniques on the children’s feet and assess the quality of their footwear by evaluating shoe sizes with scientific measurements. This will help us determine if there is a mismatch between footwear and foot size, which could potentially lead to deteriorating foot health in children. Additionally, we plan to collect data on foot pressure mapping to determine the pressure points on the children’s feet. We will evaluate their pain status based on the anatomical pain location, type, and intensity using numerical pain rating scales. 

#### 2.1.1. Study Plan

This study was initiated on 1 April 2022 and ends on 1 May 2025 (end of the project). We planned for the last visit and last subject to be on 1 January 2023. However, due to COVID, the project has been delayed. 

#### 2.1.2. Study Organization

This study is organized under the leadership of a senior medical consultant and one senior researcher who oversees the employment and supervision of a team of researchers. The team consists of three medical students (TAP), four doctors, six podiatrists, one project coordinating nurse, and one senior researcher as a collaborator. Regularly scheduled meetings are held throughout the school year, with ad hoc meetings as necessary to ensure effective coordination and collaboration among team members. This study will be conducted in collaboration with 20 schools at different locations in Region Hovedstaden and Region Sjaelland. 

## 3. Participants

A thousand children from the first, fifth, and ninth grades in Danish primary schools will be asked to participate in this study.

### 3.1. Inclusion Process

When a child enters this study, we will not intervene in any prescribed therapy and medication. We plan to include a thousand children (with a possible dropout rate of 5%), which will be possible due to a collaboration with a selected number of schools in Region Hovedstaden and Sjaelland. All participants will be recruited through the director of the participating school. One local co-investigator (not associated with this study) will be appointed from each school. The inclusion process will continue until a total of a thousand subjects are included in this study. The project coordinator and the co-investigator at each school will send out a specific link to relevant information for the possible candidates and obtain a signed informed consent. This link will be mediated via the Danish parental-school communication channel, the Aula portal. Access to Aula will be through parents or guardians who must log in with the Danish national identification service NemID. The data, which are mediated, are stored in Europe. Aula is hosted by Amazon Web Services (AWS). AWS is an American-owned company that provides cloud solutions and has data centers in Ireland, Germany, and France, among others. However, part of the Aula agreement is that data must be located in an EU/EEA country. Data in the Aula system are encrypted. Data are encrypted throughout the process. The keys to the encryption are securely stored in Denmark, and Aula complies with the GDPR rules and rules regarding IT auditing. This is mediated through a previously approved procedure in Region H for the Redcap database and a similar procedure has been approved in a project in ‘De Videnskabsetiske Komitéer for Region Midtjylland’. As mentioned, all participants will then be recruited using a method that is approved by the local information security service CIMT, region H, Copenhagen Denmark*, where we will obtain consent for a research project using the REDCap system by asking the subjects and caregivers for consent to participate in a project using the following procedure: The subject and caregiver log on to Aula with NemID.A link to RedCap is sent via Aula to the subject and caregiver (who has now been verified via the NemID login).The subject and caregiver enter RedCap to be able to assess written patient information and preliminary oral information via video, with the possibility to orally inquire about additional information on the project (see below).After this, they will be able to confirm his/her consent by signing into the digital system.

This method is applied since the Section for Information Security* assesses that the verification of the citizen that happens when the subject and caregiver must log into the e-box with their NemID to access RedCap and give his/her consent is in itself sufficient. The Section for Information Security, therefore, considers the subsequent signature with a digital device as an “extra” measure that is not decisive for the actual verification. The Section for Information Security can thus confirm that this method of obtaining consent via RedCap is legally compliant in terms of data protection law and that the method in the Capital Region is “approved”. Information will be sent to Redcap as described. Potential candidates for this study will be identified and screened for inclusion. Screening and assessments will be performed by the project coordinator and project leader to determine eligibility. As the participants in this study are minors, informed consent from both parents will be obtained after receiving written information about the study from the project coordinator as described. Written and oral information via video and the project coordinator, which will initially be provided via Redcap, will be sent/administered. The child and caregiver will be given the possibility to contact the investigators via email and phone for further information about the project and relevant information to possible candidates before giving their consent. The project coordinator will make sure that participation in this study also follows the interests of the child. Should the parents have any questions regarding this study, they can contact the project coordinator via mail or phone. If parents and/or their child(ren) do not want to participate, they can withdraw at any time during this study, thus following the local guidelines of informed consent. We will include the subjects according to the following criteria:

### 3.2. Inclusion Criteria

Children aged 6–18, and the children must attend 1st, 5th, or 9th grade at a Danish primary school.Children from selected schools in Region Hovedstaden and Region Sjælland.

### 3.3. Exclusion Criteria

Not accepting to participate in this study.Malignancies or infections discovered throughout this study that warrant acute medical treatment.

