## Abstract

Background: The health of children’s lower extremities and feet is a focus area for caregivers and healthcare professionals such as doctors, school nurses, and podiatrists. Our study aims to investigate the general health status of Danish children’s lower extremities and feet to identify anthropometric parameters that might be preconditions for pain and evaluate for foot diseases and whether they are associated with pain intensity and location, three-dimensional foot dimensions and foot pressure mapping, shoe dimensions, types and intensity of sports activity, quality of life, and foot health. The aim is that we will be able to identify parameters pre-dispositioning for pain, thus providing recommendations for sports activities in relation to the anthropometric conditions of a child as a potential preventive measure for pain. This analysis will be stratified by socioeconomic status on a group level, and this perspective will be able to provide preventative recommendations to prevent pain. Methods: This study is a cross-sectional examination of a thousand children in the first, fifth, and ninth grades in randomized selected Danish primary schools. We will perform a clinical examination of the lower extremities and feet for misalignments, deformities, and diseases as well as rotational status and range of motion. Moreover, we will evaluate their pain levels, sports activities, three-dimensional foot dimensions, plantar pressure, footwear, and patient-related outcome measures (PROMs) for foot health and quality of life. Results: We aim to provide an anthropometrical overview of the lower extremities and feet in children. The obtained basic understanding of healthy normal material in children will be analyzed for its relationships with pain level, sports activities, and socioeconomic status on a group level. This could potentially provide us with an understanding of the factors that impact lower extremity and foot diseases in children. In conclusion, examining children’s lower extremities and feet in Danish primary schools is a step toward identifying areas of improvement in self-care and shoe fitting, mapping podiatry-related needs of care in children’s feet, and providing parental recommendations for preventive actions on shoe fitting and the choice and intensity of sports activity concerning pain. Conclusions: The tenet of this study is a long-term follow-up to evaluate the long-term socioeconomic course on a group level, foot status, and sports activity, using patient-related outcome measures evaluating quality of life and other lifestyle factors such as emotional functioning, social functioning and interaction, and school functioning. Potentially, this will improve children’s quality of life and prevent future diseases.

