
## 1. Introduction

The well-being of children, and the health of children’s feet, is a priority for a range of professionals, such as school nurses, pediatricians, general practitioners, pediatric orthopedics, and podiatrists [1,2]. Social inequality impacts general health in an environment of growing social differences in an increasingly fragmented healthcare system and might raise barriers to accessing qualified health care, thus indicating a need for either rehabilitation and preventive actions or information on healthcare issues concerning children’s diseases of the lower extremities and feet, and a study evaluating the need of healthcare services indicates that this might not reach medical consultation [3,4,5,6,7]. Healthy feet are a prerequisite for many physical activities, and painful feet may inhibit children in physical exercise and give a decreased quality of life [8,9,10]. Children can have painful feet for a plethora of reasons, and structural differences may have an impact on pain and level of activity. Parents and grandparents are concerned that children with in-toeing, flat feet, and curly toes may develop pain or disability, and healthcare workers must be able to differentiate between what are merely physiological variations and what may lead to detrimental conditions as a child grows older. Previous studies indicate that children are born with “flat feet’’ [11,12,13,14] and that the longitudinal medial arch is not fully developed until a child is 6–7 years old [15,16]. Therefore, several studies have failed to show that insoles and special shoes in preschool children change the natural history of flat feet [17]. However, studies examining anthropometric parameters of the lower extremities and feet have not been performed in older children, and little is known about how this affects an older child in relation to pain and how this may affect their participation in sports and other physical activities. Children with flat feet may have a reduced quality of life, thus motivating interventions. A recent study indicates that insoles in older children may change the osseous construction of the foot and thus, may prevent painful flat feet in adults [18]. Therefore, insoles may have the potential to prevent painful flat feet in adults and potentially prevent surgery for this condition in adults [19]. For these motivating reasons, the pediatric orthopedics section of the Rigshospitalet and Hvidovre Hospital, the University of Southern Denmark, and the Association of Danish Podiatrists have started a project for the evaluation and screening of children’s feet and lower extremities in Danish primary schools. Wearing shoes can be underestimated concerning the health of children’s feet, but a too-tight-fitted shoe is known to predispose to hallux valgus and lead to foot pain in children [20,21,22]. Studies in the European setting indicate that children in these countries often wear shoes that are too small [23,24]. The effect of shoe fit also impacts the development of pathological diseases such as apophysitis of the calcanei, and simple ingrown toenails and may give rise to deformities, ingrown toenails, or non-specific foot pain [20,22,25]. In this study, we plan to evaluate this using the commercial technology of 3D surface scanning and evaluate the appropriateness of shoe fitting via the measurement of shoe size. The perspective of this study is that we, in the future, will be able to provide recommendations for preventive actions for children for improvement in the care of the health of children’s lower extremities and feet, thus demonstrating the potential for long-term health and societal financial benefits, such as referral to other health services, guidance on sensible footwear, foot care, and hygiene. The purpose of this project is to identify anthropometric parameters that might be preconditions for pain, evaluate for foot diseases and whether they are associated with pain intensity and location, three-dimensional foot dimensions and foot pressure mapping, shoe dimensions, intensity and type of sports activity, and status of quality of life and foot health according to patient-related outcome measures (PROMs). The aim is that we will be able to identify parameters pre-dispositioning for pain, thus providing recommendations for sports activities in relation to the anthropometric conditions of a child as a potential preventive measure for pain. Our purpose with this study is threefold:To make reference material of the demography of the foot, the rotational status, and the range of motion in joints in the lower extremities of children in Denmark to evaluate if these anthropometric parameters in children influence pain status.Examining the prevalence of pain in children as well as exploring the prevalence of pathologies in children’s feet to evaluate if these conditions in children influence pain status.Evaluating the appropriateness of shoe fitting using commercial 3D technology and foot pressure mapping to evaluate if shoe fitting in children influences foot pain status.

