### 3.4. Treatment during and after This Study Has Ended/Exclusion from This Study and Discontinuation of This Study

If a child is discovered to have severe pathologies such as malignancies of infection that need acute intervention during this study, then the child has to be excluded and treated. After exclusion, the child and their parents have the possibility of us sharing the discovered information (from this study) about their child’s health status as well as if we will recommend seeking medical care. If a child is being treated, we will allow the child to continue being treated. If a child participating in this study has an unexpected negative effect due to the evaluation, either according to the parents or based on the measurements performed, an assessment by the project coordinator (in collaboration with the parents) will be carried out to decide if the child should be excluded. The reason for exclusion will be reported, and it will be decided if it is still safe to continue the study. The child will continue to receive the best possible care when entering this study. 

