### 5.3. Patient-Related Outcome Measures (PROMs) and Pain Status

Our endpoints for this study are foot health, pain status, sports activity level, and quality of life. We will evaluate pain intensity and location using the ‘Chili’ score, Wong–Baker and VAS numeric rating scale, and a systematic pain drawing, respectively [28]. We will measure foot health using the validated Danish version of the Oxford Foot Score for Children (OxAFQ) and compare scores with the prevalence of foot pathologies [29]. The OxAFQ is a discriminative and evaluative tool that can differentiate between severe chronic disease and benign fluctuating disease. We will assess activity levels and the Pediatric Quality of Life (PedsQL) questionnaire. The 23-item PedsQL Generic Core Scales are designed to measure the core dimensions of health as delineated by the World Health Organization. These data will be acquired either via REDCAP via a subject’s social security number for the questionnaires, and pain status will be evaluated when a child is examined. The caregiver and child will also be asked if the child has orthopedic and other diseases.

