### 6.3. Statistical Analysis and Randomization 

Three clusters of equally divided children from the 1st grade, 5th grade, and 9th grade will be evaluated. This was chosen to embrace the spectrum of chronological (with different developmental stages) ages in Danish primary schools. The total planned number of included children is a thousand children. The sample size was chosen based on a balance between the desired statistical robustness and the practical constraints of this study. These constraints include available resources, such as funding, staffing, and logistics. This sample size is in line with or larger than similar large-scale, observational studies in pediatric populations [36,37,38], where specific power calculations can be more complex due to the multitude of variables and outcomes being explored. We acknowledge this as a limitation but also believe that the chosen sample size is sufficient to provide meaningful and robust data for the objectives of our study. The schools will be chosen randomly with the measure of crow fly distance and the number of children in the schools (>1000). A school’s socioeconomic status will be registered based on the ‘Socioøkonomisk reference for grundskolekarakterer 2018/2019′ [36]. The normality of the data will be assessed graphically using quantile–quantile and density plots. 

Based on their distribution, variables will be described using either means and standard deviations (for normally distributed data) or medians and interquartile ranges (for non-normally distributed data). Appropriate hypothesis tests will be conducted based on the distribution of the data. These include Student’s t-test and Wilcoxon’s rank-sum test for continuous data. For categorical data, chi-square tests and Fisher’s exact test will be used as appropriate. *p*-values of ≤ 0.05 will be considered statistically significant. Simple bivariate analyses will be conducted to establish initial associations between potential predictor variables and relevant outcome variables. To investigate the associations between pain and lower extremity kinematic and alignment variables, we will use multilevel multivariable logistic regression models, stratified by grade (1st, 5th, and 9th). Examiner ID will be included as a random factor in the models. The statistical analysis will be performed using the newest available version of R [39].

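### Children with acute findings are excluded from a study that estimates the prevalence of foot pathology, and the stated summaries give no outer reference limits for non-normal measures

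*Protocol article*

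**What the plan says.** The Introduction gives three purposes. The first is reference material on the foot, rotational status and joint motion for children in Denmark. The second begins "Examining the prevalence of pain in children as well as exploring the prevalence of pathologies".

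Section 3.2 includes children by age, grade and school, with no health criterion. Section 3.3 excludes those who decline and also "Malignancies or infections discovered throughout this study that warrant acute medical treatment". Section 3.4 words the same rule a little more widely: it speaks of severe pathologies, with malignancy and infection as examples, "that need acute intervention during this study, then the child has to be excluded and treated". Later in section 3.4, on children with an unexpected negative effect of the evaluation, it adds: "The reason for exclusion will be reported, and it will be decided if it is still safe to continue the study". Neither section says whether data already collected from an excluded child stay in the analysis.

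Section 6.3 describes variables by means and standard deviations if normally distributed, or by "medians and interquartile ranges (for non-normally distributed data"). It names no other descriptive summary.

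The Abstract says: "The obtained basic understanding of healthy normal material in children will be analyzed". Section 5.3 says: "The caregiver and child will also be asked if the child has orthopedic and other diseases". Section 6.3 gives the answer to that question no role.

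**The concern.** In a prevalence study the examination produces the outcome. A rule that removes a child because of the examination result removes only cases, and those with acute disease. The estimate is then too low, and any link between that pathology and pain is estimated without those children.

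The second issue is what a reader can do with the reference material. A clinician who wants to know whether a child's hip rotation is unusual needs outer limits. Mean and SD supply them when a variable is close to normal. A median with an interquartile range does not.

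The third is the target of the reference values. The Introduction points to all children in the country, while the Abstract calls the material healthy. The two descriptions imply different samples.

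**Working it through.** The article derives no figure on these points, so there is nothing of its own to reproduce. The planned total of 1000 children in three equal grade groups (sections 3.1 and 6.3) is used as given, about 333 per grade. All case counts, disease shares and shifts below are assumptions.

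**1. Effect of the exclusion on prevalence.** With c true cases among 1000 examined children and a of them excluded, the observed prevalence is (c − a)/(1000 − a).

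| True cases | Excluded | Observed | True | SE of true prevalence |
|---|---|---|---|---|
| 50 | 1 | 49/999 = 4.90% | 5.00% | 0.69 points |
| 50 | 2 | 48/998 = 4.81% | 5.00% | 0.69 points |
| 50 | 5 | 45/995 = 4.52% | 5.00% | 0.69 points |
| 50 | 10 | 40/990 = 4.04% | 5.00% | 0.69 points |
| 20 | 1 | 19/999 = 1.90% | 2.00% | 0.44 points |
| 20 | 10 | 10/990 = 1.01% | 2.00% | 0.44 points |

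The SE is √(p(1 − p)/1000); for p = 0.05 this is √(0.05 × 0.95/1000) = 0.0069.

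Which rows are realistic depends on how many cases meet the rule. Section 5.2 maps warts, deformities, ingrown toenails, callosities, hallux valgus and metatarsus varus, among others. Nearly all of these do not call for acute treatment. The rows with one or two exclusions are therefore the plausible ones for most conditions. The larger losses would need a condition that is often acute. If every case of a rare condition met the rule, its reported prevalence would be zero.

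**2. What the stated summaries cover.** For a normal variable the interquartile range spans ±0.67 SD and holds 50% of children. A 95% reference range spans ±1.96 SD. For a skewed variable the outer limits cannot be recovered from the quartiles.

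**3. Precision of outer percentiles.** For a normal variable the SE of the 97.5th percentile is √(0.975 × 0.025/n)/φ(1.96), in SD units. With n = 333 this is 0.146 SD, so the 95% confidence interval is about ±1.96 × 0.146 = ±0.29 SD. About 333 × 0.025 = 8 children per grade lie beyond each limit. The calculation ignores clustering by school.

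**4. How much the meaning of normal matters.** Let a share f of children have a disorder that shifts a measure by d SD, with the same SD. The 97.5th percentile x solves (1 − f)Φ(x) + fΦ(x − d) = 0.975; without diseased children x = 1.96.

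| f | d = 1 | d = 2 |
|---|---|---|
| 1% | 1.98 | 2.05 |
| 5% | 2.08 | 2.40 |
| 10% | 2.18 | 2.76 |

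The limit moves by 0.02 to 0.80 SD, from well inside one SE (0.146 SD) to more than five. The article gives no figure for f or d.

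**The case against.** The strongest reply on prevalence is that exclusion in section 3.4 may mean only that the child stops being examined and is sent for care. The article does not say that data are deleted, and it says findings can be shared with the family after exclusion, so they are kept at least for that. The rule is also narrow. Both points stand as limits on size. They do not remove the issue, because the article states an exclusion outright and the plain reading takes the child out of the sample.

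A reader might infer that the most severe pathology in general is removed, or that 10% to 20% of a condition's cases would be lost. The documents do not support either: the rule is tied to the need for acute intervention, and no figure is given for how often that arises.

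On the summaries, section 6.3 uses standard descriptive wording, and a condensed article need not list every percentile. That stands. A reader might conclude that no usable reference limit will be reported. This does not follow, since mean and SD give limits for normal variables and the article does not rule out percentiles.

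On the reference population, it is tempting to say that diseased children wrongly contaminate a healthy reference set. The Introduction defines the reference by country, not by health. The healthy label appears only in the Abstract. References elsewhere to typically developed children concern the pilot children (section 6.4) and background (section 7). A reference for all schoolchildren is a legitimate choice, and inclusion by age, grade and school fits it.

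**Conclusion.** The point holds in a limited form.

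- **Prevalence.** Followed as written, the exclusion selects on the outcome and biases prevalence downward. The effect is probably slight, of the order of 0.1 to 0.2 percentage points on a 5% prevalence if one or two of 50 cases are lost. It falls mainly on infection-related findings. It could matter for a rare condition that is usually acute.
- **Summaries.** The stated summaries give no outer limits for non-normal variables, although the study is meant to supply reference material. This is a cheap improvement to make, not a demonstrated error.
- **Meaning of normal.** The Abstract and the Introduction describe different reference populations. This needs consistent wording. It does not show that the sample is wrong for either.

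**What to change.** 1. State in sections 3.3 and 3.4 that every examined child, including one referred for an acute finding, stays in the numerator and denominator for prevalence with data up to the finding. This concerns the analysis only and leaves clinical handling as it is. Cost: one sentence.
2. Add to section 6.3 that reference measures will be reported as 2.5th, 50th and 97.5th percentiles with 95% confidence intervals by grade, alongside the summaries already named. Cost: a little more analysis, and outer limits that are imprecise at about 333 children per grade. The intervals make that visible.
3. Choose one meaning of normal and use it in the Abstract, the Introduction and section 5.2. If the reference is for all schoolchildren, drop the word healthy. If wanted, add a sensitivity analysis without children whose caregivers report orthopedic disease, using the question in section 5.3. That question is broad and may identify such children imperfectly, so the analysis should supplement the main reference values and need not replace them.

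Section 6.1 says that the dataset has been generated and is under preliminary analysis, so these choices should be written down before prevalence and reference values are finalised.
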